### Outcomes

The primary outcome is the incidence of diarrhea defined according to the WHO definition (greater than 3 liquid bowel movements in 24 hours) any time during the index ICU admission (Table 1). This will be identified from nursing flowsheets in EPIC. The secondary outcomes include mortality (ICU and hospital), length of stay (ICU and hospital), incidence of confirmed or suspected hospital-acquired blood stream infections or central line associated blood stream infections, incidence of aspiration pneumonia/pneumonitis (identified pragmatically as documented by the ICU team), CDI, percentage of caloric requirements received by enteral nutrition (daily caloric requirements defined as 25 kcal/kg/day1 and by registered dietician assessment), incidence of vomiting, ileus and abdominal distention, and glycemic control (using average daily insulin dose and average daily glucose as a surrogate) (Table 1).

### Sample size

As this is a retrospective study, our sample is dependent on the number of patients who are eligible and classified in each of the IEN and CEN groups. On initial review of the EMR at each site, we expect that approximately 500 patients at HHS and SJHH meet the inclusion criteria. We suspect that the number of patients receiving IEN will be less than that of those receiving CEN.

A recent meta-analysis of observational studies including 717 patients across 11 studies found that 25.1% of patients on IEN developed diarrhea while only 17.5% on CEN had diarrhea [18] Using a two-tailed z-test approximation of independent proportions with a power 0.8 and alpha of 0.05, we estimate that each group would require 455 patients [19]. Given this calculation we suspect that the study will be adequately powered for the primary outcome of interest.

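### The sample-size section calls the study adequately powered, but 455 per group cannot come from about 500 patients: power is at most about 55%, not 80%

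*Protocol article*

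**What the plan says.** All the relevant statements are in the Sample size section of the protocol article.

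- Expected sample: "we expect that approximately 500 patients at HHS and SJHH meet the inclusion criteria".
- Balance of the groups: "We suspect that the number of patients receiving IEN will be less than that of those receiving CEN". No split is given.
- Planning effect: a meta-analysis of observational studies "found that 25.1% of patients on IEN developed diarrhea while only 17.5% on CEN had diarrhea".
- Test and error rates: "Using a two-tailed z-test approximation of independent proportions", "with a power 0.8 and alpha of 0.05".
- Requirement: "we estimate that each group would require 455 patients".
- Conclusion: "Given this calculation we suspect that the study will be adequately powered for the primary outcome of interest".

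Two other sections bear on how many patients can contribute. Participants admits patients on prolonged non-invasive ventilation (NIPPV) who were never prescribed enteral nutrition. Data analysis puts a patient in the IEN group only after two complete days on IEN and IEN on most study days.

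**The concern.** Two groups of 455 make 910 patients, and the section expects about 500. If one group did reach 455, only about 45 would be left for the other. The expected imbalance lowers power further. The calculation therefore points to an underpowered comparison, yet it is cited as the reason for calling power adequate.

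What is at stake is how a null result is read. The Introduction describes the effect of feeding strategy on diarrhea as unclear and cites trials that found no significant difference. Strengths and limitations says this study will support and inform post hoc work from an upcoming randomised trial. A non-significant result from a study labelled adequately powered would look like further evidence of no difference. In fact the study would have about an even chance, or less, of detecting its own planning effect.

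**Working it through.** **Inputs (Sample size section).** p1 = 0.251 (IEN), p2 = 0.175 (CEN), difference d = 0.076, two-sided alpha 0.05 (z = 1.960), power 0.80 (z = 0.842), expected total 500. The IEN share is not stated, so it is varied here as an assumption.

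**Step 1: reproduce the 455.** Two-sided z-test with pooled variance under the null and no continuity correction, p̄ = (0.251 + 0.175)/2 = 0.213:

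n = [1.960·√(2·p̄(1−p̄)) + 0.842·√(p1(1−p1) + p2(1−p2))]² / d²

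= (1.1349 + 0.4852)² / 0.076² = 454.4, rounded up to **455 per group**.

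The figure reproduces. The unpooled and arcsine versions give 451.7 and 452.3 before rounding. Power at 455/455 is 80.05%.

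**Step 2: compare with the expected sample.** Required: 2 × 455 = 910. Expected: about 500. 500/910 = 55%.

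**Step 3: power with 500 patients.** For n1 on IEN and n2 on CEN:

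- p̄ = (n1·p1 + n2·p2)/(n1 + n2)
- s0 = √[p̄(1−p̄)(1/n1 + 1/n2)]
- s1 = √[p1(1−p1)/n1 + p2(1−p2)/n2]
- power = Φ[(d − 1.960·s0)/s1]

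At 250/250: s0 = 0.03662, s1 = 0.03646, (0.076 − 0.07177)/0.03646 = 0.116, power = 54.6%.

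At 100/400: s0 = 0.04388, s1 = 0.04734, (0.076 − 0.08600)/0.04734 = −0.211, power = 41.6%.

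The expected half-width of the 95% confidence interval for the risk difference is 1.960·s1. The detectable IEN rate is the value of p1 that gives 80% power against 17.5%.

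| IEN/CEN | IEN share | Power | IEN rate detectable at 80% power | 95% CI half-width (points) |
|---|---|---|---|---|
| 250/250 | 50% | 54.6% | 28.0% | 7.1 |
| 200/300 | 40% | 53.9% | 28.1% | 7.4 |
| 150/350 | 30% | 49.8% | 28.8% | 8.0 |
| 100/400 | 20% | 41.6% | 30.5% | 9.3 |
| 75/425 | 15% | 35.7% | 32.1% | 10.5 |
| 50/450 | 10% | 28.2% | 34.9% | 12.5 |

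Over all splits of 500 the maximum is about 55%. The half-width is close to the 7.6-point planning effect at an even split and exceeds it at a 30% IEN share or less. For the unequal splits the unpooled and arcsine approximations give lower power than the table (36% and 38% at 100/400), so the choice of formula does not help the claim.

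**Step 4: total needed for 80% power.** About 910 at a 50% IEN share, 1,058 at 30% and 1,371 at 20%.

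**Step 5: alternative reading, 500 at each organisation (1,000 in total).**

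| IEN/CEN | Power |
|---|---|
| 500/500 | 83.6% |
| 350/650 | 80.7% |
| 300/700 | 77.8% |
| 200/800 | 67.5% |

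The 80% mark is reached only when IEN makes up about 34% or more of the patients compared.

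**The case against.** The strongest objection is that the total is ambiguous. The sentence giving 500 opens by referring to a review of records at each site, and Pilot testing and Data adjudication treat the two organisations as the two sites. At 500 per organisation the total is 1,000 against 910 needed, which would explain the authors' conclusion. This deserves an explicit answer from them, but it does not rescue the sentence. The wording gives one number for both organisations together. Even 1,000 is enough only with about a third or more on IEN, and the section states no share while expecting IEN to be the smaller group.

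It is also fair that only the 55% ceiling follows from the article's own figures. The 42% and lower values rest on assumed IEN shares. Likewise, no count is given for NIPPV patients without enteral feeding, so only the direction of that effect is known.

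Finally, the sample is retrospective and fixed, the claim is hedged, and results are already to be reported with 95% confidence intervals. That limits the remedy to wording, but it does not make the statement right. The authors chose a two-group test, calculated a requirement and drew a conclusion that the requirement contradicts. The plan also includes between-group chi-square comparisons, so power is relevant.

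**Conclusion.** The concern holds, and the sentence must be corrected. The 455 per group is right; the conclusion drawn from it is wrong. With about 500 patients in total, power for 25.1% versus 17.5% at two-sided alpha 0.05 is at most about 55%. It is about 50% and 42% if the IEN share is 30% or 20%.

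This rests on reading 500 as the combined total, on the article's own planning rates, and on all 500 being classifiable as IEN or CEN. The last assumption is generous, because the inclusion criteria admit patients who receive no enteral feeding. If 500 is per organisation, adequacy depends on an IEN share of about 34% or more among enterally fed patients, which nothing in the article supports. No other section repairs the contradiction.

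**What to change.** 1. Delete the sentence claiming adequate power.
2. State whether 500 is the combined total or the number per organisation, and give the expected count of enterally fed patients who can be classified as IEN or CEN, leaving out NIPPV patients without enteral nutrition.
3. If the total is about 500, say that power for 25.1% versus 17.5% is at most 55%. Give a short table of power, detectable difference and expected confidence interval width at IEN shares of 50%, 30% and 20%. The working above supplies those rows for 500 patients; recompute them if the count differs.
4. Say that the comparison will be interpreted from the effect estimate and its 95% confidence interval, and that a non-significant result will not be taken as evidence of no difference.

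The cost is one reworded paragraph and a less favourable power statement. No patients are added, and data collection and the analysis are unchanged.

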### Pilot testing

We will begin with an iterative process of 40 randomly selected patients, 20 from each site. This will allow us to review and refine the reports generated by the IT service teams. Each of the 40 charts will be adjudicated by two reviewers to determine the accuracy of IT reports. We will adjudicate on the primary and secondary outcomes, and key clinical data including mode of nutrition, timing of nutrition, and mode of ventilation. This will operationalize the suitable patient identification for this study, identify any challenges needing to be addressed before embarking on the study in the operations or case report forms and it will help to enhance the validity of our data. Once optimized we will only manually review charts for missing/unclear data.

### Data adjudication

To assure the accuracy of our data, a second round of adjudication after the pilot exercise and after data collection will be performed. A total of 50 patients will be randomly selected from SJHH and HHS (25 from each site). Each of the charts will be adjudicated by two adjudicators. Adjudication will again be performed as explained above for pilot testing. This data will be compared to that generated from reports to ensure agreement.

For the secondary outcomes patients also be divided into those who have received NIPPV and those who have not. For the purposes of this study, NIPPV will exclude HFNC but will include bilevel positive airway pressure (BiPAP) and continuous positive airway pressure (CPAP) delivered via any interface. To evaluate the relationship between IEN, CEN and NIPPV on caloric goals, each patient’s caloric intake at 48 hours and 7 days will be divided by their 24 hour caloric target (as determined by RD assessment and by the algorithm 25 kcal/kg) (Table 1). The average of these percentages with associated 95% CI will be calculated in each group. The proportion of patients in each group receiving supplement parenteral nutrition at these time points will also be determined to help evaluate the effectiveness of each EN strategy (Table 1). Logistic regression will also be applied to evaluate the role of covariates; specifically baseline characteristics and the effect they may have on patients reaching their caloric targets (Table 1). In terms of other secondary outcomes, the incidence of hospital acquired infections, ICU and hospital mortality will be determined per person-time at risk in each group (IEN vs CEN) with associated 95% CI. Significant differences between groups will again be determined by two sample t-test. Multivariate logistic regression will evaluate associations between baseline characteristics and the type of EN chosen.

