## Introduction

Over the last thirty years, nutrition in the intensive care unit (ICU) has evolved from supportive therapy to an active treatment that can attenuate the harms of critical illness [1]. Early nutrition, delivered enterally, has become the standard of care for most critically ill patients and is recommended by the major organizations for clinical nutrition and critical care [1–4]. Enteral nutrition (EN) offers many physiological benefits throughout the gastrointestinal (GI) tract, including maintenance of intraepithelial junctions, mucosal lymphoid tissues, and villous height and lower infection risk by preventing bacterial translocation [5]. Furthermore, clinical studies have demonstrated a benefit with a recent meta-analysis by the European Society of Intensive Medicine (12 randomized controlled trials (RCTs), 597 patients) demonstrating a reduction in infectious morbidity when EN was delivered within 48 hours of ICU admission [3]. Another meta-analysis, including 6 RCTs and 5025 critically ill patients, showed a reduction in mortality with early EN compared to parenteral nutrition (PN) [4]. Despite this and guidelines recommending early initiation of EN, malnutrition in ICUs continues to be a problem with 56–68% of patients in Canadian ICUs being underfed relative to their calculated caloric requirements [6].

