To determine risk factors associated with diarrhea during ICU admission	**Dependent Variable** WHO-defined diarrhea	Age, sex, type of nutrition (IEN/CEN), antibiotics, GI comorbidities, vasopressor/inotropes, daily caloric intake, NIPPV, surgical/trauma/medical admission	Logistic Regression
Secondary Outcomes			
**Research Objectives**	**Outcome**	**Covariates/Subgroups**	**Analytical Approach**
To determine whether IEN or CEN is better for reaching caloric requirements during ICU stay	**Dependent Variables:** Average caloric intake (percent goal determined by RD or 25 kcal/kg) at 48 hours and 7 days after initiation of CEN/IEN Proportion of patients on PN at 48 hours and 7 days after initiation of CEN/IEN	NIPPV, Age, sex, antibiotics, GI comorbidities, type of nutrition (IEN/CEN) vasopressor/inotropes, daily caloric intake, surgical/trauma/medical admission	Descriptive statistics (average caloric intake) and corresponding 95% CI Descriptive statistics (proportion of patients on PN) and corresponding 95% CI Logistic regression
To determine whether IEN or CEN is associated with ICU-acquired bloodstream infection or *Clostridium difficile* infection	Incidence of positive blood cultures drawn at least 48 hours after admission, excluding coagulase-negative staphylococcus unless suspected by ICU team to not be contaminant.	NA	The incidence of bloodstream infections will be computed as the number of new cases during ICU stay divided by the person-time at risk. Descriptive statistics (proportion of patients with ICU-acquired bloodstream infection or *C. difficile infection*) and corresponding 95% CI
To determine whether IEN or CEN is associated with differences in mortality or length of stay (ICU or hospital)	**Dependent Variables** Mortality (ICU and hospital) Length of stay (ICU and hospital)	Age, sex, type of nutrition (IEN/CEN), antibiotics, GI comorbidities, vasopressor/inotropes, daily caloric intake, NIPPV, surgical/trauma/medical admission	Descriptive statistics (mortality and length of stay) and corresponding 95% CI Logistic regression

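### Caloric adequacy is reported as a continuous percent of goal, but the only model named is logistic regression on an undefined reached-target event, so the adjusted and reported results concern different endpoints

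*Protocol article*

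**What the plan says.** In Table 1 of the protocol article, the row on meeting caloric requirements has two dependent variables. The first is "Average caloric intake (percent goal determined by RD or 25 kcal/kg) at 48 hours and 7 days after initiation of CEN/IEN". The second is "Proportion of patients on PN at 48 hours and 7 days after initiation of CEN/IEN". For the first, the analytical approach column gives "Descriptive statistics (average caloric intake) and corresponding 95% CI". The same column then lists logistic regression without saying which dependent variable it serves. The row's covariates include feeding mode and also daily caloric intake.

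The Data analysis section divides each patient's intake by a target, "as determined by RD assessment and by the algorithm 25 kcal/kg", and continues: "The average of these percentages with associated 95% CI will be calculated in each group". It then states: "Logistic regression will also be applied to evaluate the role of covariates", meaning baseline characteristics and "the effect they may have on patients reaching their caloric targets". The Outcomes section also lists this endpoint as a percentage of requirements. No linear or other continuous-outcome model is named anywhere for percent of goal.

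**The concern.** An ordinary logistic model needs a binary outcome. The outcome as defined and summarised is a percentage. The text supplies a binary event only in passing, and that event appears in neither the outcome column of Table 1 nor the Outcomes section.

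Three things follow.

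- The unadjusted comparison would be a difference in mean percent of goal, while the adjusted one would be an odds ratio for a different endpoint. A reader could not tell whether a change between them reflects control of confounding or the switch of endpoint. The Strengths and limitations section itself warns that differences in caloric intake may be due to covariates and illness severity, so adjustment matters here.
- With the threshold, time point and target open, the event could be settled after the data are seen.
- A cut at the target counts a patient at 95% of goal and one at 20% as the same failure, which costs precision in the regression.

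Separately, daily caloric intake is listed as a covariate for an outcome of which it is the numerator.

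**Working it through.** **The plan's own figures.** The protocol gives no sample size, power or effect size for caloric adequacy. Its one calculation, 455 per group, is for diarrhea (25.1% vs 17.5%, two-sided 0.05, power 0.80). It reproduces: [1.960·√(2·0.213·0.787) + 0.842·√(0.251·0.749 + 0.175·0.825)]² / 0.076² ≈ 454.4, rounded up to 455. It has no bearing on this point.

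**The statements side by side.**

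- Outcomes section: a percentage of requirements (continuous).
- Table 1, outcome column: mean percent of goal (continuous) and parenteral nutrition use (binary).
- Table 1, approach column: mean with 95% CI, proportion with 95% CI, and logistic regression with no outcome assigned.
- Data analysis text: mean of the percentages by group (continuous), then logistic regression tied to reaching caloric targets (binary, undefined).

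The mismatch therefore sits inside Table 1 and again inside the text. Even if reaching is read as at least 100%, two targets × two time points leave 2 × 2 = 4 candidate events, and none is chosen.

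**Information lost by a cut.** Assume percent of goal is normal with equal variance in the two groups. If a share p reaches target, the efficiency of the binary analysis relative to the continuous one is φ(z_p)² / [p(1−p)], where φ is the standard normal density and z_p the p-quantile.

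The only figure in the protocol that bears on p is in the Introduction: "56–68% of patients in Canadian ICUs being underfed relative to their calculated caloric requirements". Its complement is 100 − 68 = 32% to 100 − 56 = 44%. Using this as the share reaching target is an assumption.

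- p = 0.50: 0.3989² / 0.25 = 0.637, a loss of 36.3% (the smallest possible)
- p = 0.44: 0.3944² / 0.2464 = 0.631, a loss of 36.9%
- p = 0.32: 0.3576² / 0.2176 = 0.588, a loss of 41.2%
- p = 0.20: 0.2800² / 0.16 = 0.490, a loss of 51.0%

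**What that means for power (illustration only).** Take a difference detectable with 80% power on the continuous scale, so that its standardised size is 1.960 + 0.842 = 2.802. After the cut, power is Φ(2.802·√efficiency − 1.960):

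- p = 0.44: Φ(0.266) = 60.5%
- p = 0.32: Φ(0.188) = 57.4%

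Direct two-proportion calculations use 500 patients in assumed splits. With 250/250 and a shift of 2.802·√(2/250) = 0.251 SD, power is 60.7% and 58.8% for the same two values of p. With 125/375 and a shift of 0.289 SD, it is 60.8% and 60.1%. All of these are unadjusted two-group figures.

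**The case against.** The strongest reply is that a binary endpoint suits the stated objective, which is about reaching requirements. On this view the target is given, reaching naturally means 100% or more, and the remaining detail belongs in a fuller document. The row's second dependent variable, parenteral nutrition use, is binary and suits logistic regression. The text also presents the model as an examination of baseline covariates, not as the headline comparison of feeding modes.

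Part of this stands. Logistic regression does have a proper use in that row, and a reached-target outcome is a legitimate thing to want. But the text ties the logistic model to caloric targets, not to parenteral nutrition. Feeding mode is among the row's covariates, so this is the only named model that would give an adjusted feeding-mode effect on intake. The protocol does not merely omit detail: it states the outcome, the summary and the model, and the model does not fit the outcome.

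Several stronger readings are tempting but unsupported.

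- A reader might infer that the plan discards a fixed share, say 40%, of the information. The protocol gives no such figure. The range above needs normality, which is doubtful for intake bounded at zero, and a background figure with no stated threshold or feeding day.
- A reader might infer that the whole caloric analysis loses precision. The group means with their intervals keep all the information.
- A reader might infer that the mean difference and the odds ratio could point in opposite directions. Under the equal-variance normal shift used here they must share a sign, and nothing in the protocol suggests otherwise.
- A reader might infer that Table 1 contradicts the text. Both contain the same mismatch.

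**Conclusion.** The point holds as a mismatch between outcome and model for a secondary outcome. Percent of goal is what the protocol defines and reports, the only model named cannot be fitted to it, and the binary event that would make the model fit is undefined in threshold, time point and target. This conclusion rests on the text alone.

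The size is conditional. If the percentage is dichotomised and is roughly normal, the regression loses at least 36% of the information at any cut-off. The loss is 37–41% if 32–44% of patients reach target, and about half if only 20% do. The power figures, 80% falling to about 57–61%, rest further on an effect chosen to give 80% power and, for the direct calculations, on assumed group splits. The change is worth making before analysis, but the primary outcome is not affected.

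**What to change.** In the caloric row of Table 1 and in the Data analysis section:

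- Model percent of goal at 48 hours and at 7 days by linear regression with robust standard errors, on feeding mode and the baseline covariates. Run it separately for the dietitian target and the 25 kcal/kg target. The adjusted difference in mean percent then matches the reported group means.
- Remove daily caloric intake from the covariates for this outcome, because it is the outcome's numerator.
- State that logistic regression in this row is for parenteral nutrition use.
- If a reached-target outcome is also wanted, label it supplementary and fix its threshold, target and time point before the data are examined.

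The cost is analysis wording only. No new data are needed.
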